**Table 1 Tab1:**
[figure not shown]
Interventions and outcome measures at specified time points

*BLISS*, Baby-led Introduction to SolidS; *PLW*, Parent-Led Weaning, *CRC*, Clinical Research Center; *CRP*, C-reactive protein; *BEBQ*, Baby Eating Behavior Questionnaire; *CEBQ*, Child Eating Behavior Questionnaire; *CFSQ*, Caregiver Feeding Style Questionnaire; *DEBQ*, Dutch Eating Behavior Questionnaire; *MCH-FS*, Montreal Children’s Hospital Eating Scale; *SLP*, Speech-Language Pathologists

At the same visit, speech therapists will advise on choking prevention, showing videos with examples of choking and gagging. All advice will be standardized; each group will have its own set of printed material of topics to be addressed by the professional, and each participant will receive a copy to take home. The major differences between the intervention groups are the consistency of foods and the level of adult participation during each meal. The basic information that every group will receive during the first intervention is:
Encouragement to breastfeed exclusively for 6 months and continue breastfeeding to at least 24 months or longer.Not to start CF until their infant is 6 months of age.Make sure the infant is always sitting upright and under adult supervision when they are eating.Specific food techniques to improve food bioavailability of iron and energy.Avoid offering honey, sugar, caffeine, juice, processed foods, and low-energy foods, such as soups, in the first 2 years of life.At age 6 months, offer a fruit at two different times plus one main meal (lunch) and, by 7 months, introduce a second main meal (dinner).Not to sift and/or liquefy any type of food.Not to offer hard foods such popcorn or nuts, nor any foods that might become sticky in the mouth, such as peanut butter.

After the first intervention, every mother will receive a dietitian’s personal phone number to call if they have questions related to the study or the CF process.

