Second, a home visit at 9 months of age will serve to measure anthropometric parameters of the mother and child. At this time, questionnaires will also be administered and any extra individualized advice or support for the CF process will be provided, always appropriate for the approach to which each mother-child pair was allocated. The visits will be led by two blinded researchers; to avoid unblinding, one will obtain anthropometric measurements before the other applies the questionnaire, as some answers given might reveal the allocation group. The visit will end with a thank-you card, to motivate family engagement with the study.

Finally, the last intervention will be conducted at the HCPA Clinical Research Center (CRC). Blood samples will be drawn for measurement of plasma ferritin, C-reactive protein (CRP), and a complete blood count, as well as saliva for genetic tests. Anthropometric measurements will be repeated, an intraoral examination will be performed, and the end-of-study questionnaires will be administered, as well as a flavor preference test. Mothers will then receive a booklet with advice on healthy nutrition and oral habits, such as nutritional assessment, oral evaluation, and oral hygiene guidance; blood test results; and nutritional guidelines for the child’s further years to come, encouraging them to continue to pay attention to healthy eating.

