### Choking

At the 9-month and 12-month visits, choking and gagging will be assessed by specific questions regarding frequency, a description of which food or drink and consistency was involved, how many times it occurred and maneuvers used to resolve the episode. Researchers will be trained to make sure they are able to distinguish a gagging event from a choking event while applying the questionnaire. We also hope the video examples shown to participants during the first intervention will help them distinguish between the two when reporting events to the researchers.

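### The gagging-versus-choking call is made in an interview whose answers might reveal the arm, so choking is open to arm-dependent misclassification in either direction

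*Protocol article*

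**What the plan says.** - **Status of the outcome.** Outcome measures lists choking prevalence among the secondary outcomes. Adverse events names choking and growth faltering, and says choking will be picked up through the questionnaires.
- **Who makes the call, and when.** Under Choking, for the 9- and 12-month visits: "Researchers will be trained to make sure they are able to distinguish a gagging event from a choking event while applying the questionnaire". The article adds a hope that the videos shown at the first intervention will help mothers tell the two apart when they report.
- **What is asked in the same block.** After frequency, the items include "a description of which food or drink and consistency was involved, how many times it occurred and maneuvers used to resolve the episode".
- **What separates the arms.** Study groups, in the text after Table 1: "The major differences between the intervention groups are the consistency of foods and the level of adult participation during each meal".
- **What is protected.** For the 9-month home visit, Study groups says "The visits will be led by two blinded researchers", and that "one will obtain anthropometric measurements before the other applies the questionnaire, as some answers given might reveal the allocation group". The same visit provides individual advice, "always appropriate for the approach to which each mother-child pair was allocated".
- **Other items at these visits.** Dietary assessment records consistency and who fed the child at 9 and 12 months. Questionnaires adds feeding practices at both visits and, at 12 months, the acceptability of the assigned method.

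**The concern.** The article recognises that the questionnaire can unblind and responds by taking the body measurements first. That is sound for weight and length. It does nothing for an outcome judged by the person who hears the answers, and the gag/choke distinction is such an outcome. The choking block itself asks about one of the two features that mainly distinguish the arms.

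The Background section on choking says that gagging is a normal reflex and must be kept apart from choking, so confusing the two is a foreseeable error. If it is equally common in every arm, it blurs the comparison but does not by itself favour an arm. If it depends on what the interviewer believes about the arm, it can produce a difference that is not there or mask one that is. Choking is a concern that the Background raises about self-feeding, so a distorted comparison would bear on how the trial is read.

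**Working it through.** The plan gives no choking or gagging rate and no power for choking, so there is no stated figure to reproduce. The check has two parts.

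**1. The sections side by side**

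1. Choking places the distinction inside the interview, with the interviewer.
2. The same block asks for "a description of which food or drink and consistency was involved".
3. Study groups makes consistency one of the two major differences between arms. The other is adult participation, and Dietary assessment asks who fed the child at the same visits.
4. Study groups orders the 9-month visit as it does "as some answers given might reveal the allocation group". The measurements come before the questionnaire; the gag/choke call is made within it.
5. Arm-specific advice cannot be given without knowing the arm, so at least one person at the 9-month visit must know it by then. This sits badly with the statement that both visitors are blinded.
6. Randomization says in general terms that assessors are blinded. Given steps 2 to 5, that cannot be relied on once the questionnaire begins.

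**2. How large the distortion could be (all rates assumed)**

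Let c be the true proportion choking, g the proportion with gagging only, and m the chance that a gag-only infant is recorded as choking. Then

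recorded choking = c + g × m.

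With c = 10% and g = 60% in every arm, and m = 0 in the comparator:

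| Extra m in one arm | Recorded there | Comparator | Ratio |
|---|---|---|---|
| 5% | 0.10 + 0.60 × 0.05 = 13% | 10% | 1.3 |
| 10% | 0.10 + 0.60 × 0.10 = 16% | 10% | 1.6 |

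At 48 per arm (Sample size), the 6-point gap is 48 × 0.06 ≈ 3 infants. By the normal approximation for two proportions, two-sided 5%, the chance of p < 0.05 with no true difference is about 14% for 16% against 10%, and about 7% for 13% against 10%.

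Varying the assumptions: c from 10% to 35%, g from 30% to 50%, and m of 5% in one arm against 15% or 25% in the other, or 10% against 30%. The spurious difference is then 3 to 10 percentage points, the risk ratio about 1.08 to 1.80, and the rejection rate about 6% to 25%. With equal m in both arms the difference is 0 and the rejection rate 5%.

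**The case against.** **The order of questions and a written definition belong to the questionnaire and the operating procedures, which are not shown.** This is fair. Quality control says that such procedures and a flowchart of topics exist, and a masked coding step might exist too. The article does, however, state who distinguishes the events and when, and the safeguards it describes for that step are training and the videos. Training to tell two events apart does not remove the influence of knowing the arm. The point rests on that stated procedure, not on something left out.

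**The interviewer may not learn the arm.** This stands in part. The article says only that some answers might reveal it. The mixed arm uses both consistencies, the parent-led arm moves to family texture by 12 months, and adherence is uncertain. One episode need not identify one of three arms. A reader might infer that the interviewer will usually know the arm; the documents do not support that.

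**The data could be recoded.** This also stands in part. Food, number of episodes and manoeuvres are recorded, so a sensitivity analysis, for example of episodes that needed a manoeuvre, is possible. It would be too strong to say that the trial could never tell bias from effect. Such an analysis would still use descriptions taken down by the same interviewer.

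**The mother is unblinded and sorts events before the interviewer hears of them.** This stands in full. Masking the coder removes the interviewer's share of the bias only.

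**Conclusion.** The concern holds as a weakness in how a secondary outcome and named adverse event is ascertained. The gag/choke call is made where the arm might become known, and the protection described covers only the anthropometry.

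The size is unknown. The 13% to 16% against 10% rests wholly on assumed rates and assumed differences in labelling, and shows scale, not what will happen. The direction is not fixed.

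Three stronger readings should be avoided:

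- **Choking as the main safety outcome.** The article does not call it that. It is one of many secondary outcomes and one of two named adverse events.
- **Leniency towards one arm hiding an excess as large as over-labelling creates.** The arithmetic differs, because leniency relabels true chokers, not the larger gag-only group. With true choking at 16% against 10%, relabelling 10% of the chokers hides 0.16 × 0.10 = 1.6 points, not 6. Hiding all 6 would need 0.06 / 0.16 = 37.5% relabelled.
- **A threat to the primary outcome.** At 9 months the anthropometry is taken before the questionnaire, and this point does not touch it.

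The change is worth making because it is cheap and removes the avoidable part of the bias.

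**What to change.** At the 9- and 12-month visits:

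1. Put the choking block before the feeding-practice, dietary and acceptability questions, and before any arm-specific advice.
2. Within the block, first record the objective description of the episode and the manoeuvres used. Fix the gag/choke code against a written definition. Only then ask about the food and its consistency.
3. Alternatively, leave the interview as it is and have an existing team member code the written descriptions later against the same definition, with food, consistency, feeder and arm masked. Adherence already has a second researcher analysing the answers to the 7-month call.
4. Reconcile the statement that both 9-month visitors are blinded with the arm-specific advice given at that visit.
5. State as a limitation that the mother knows her arm and reports the events.

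The cost is a changed question order, a short coding rule, brief retraining (Quality control already provides for periodic training) and, under step 3, a little coding work. No visit, measurement or staff member is added.

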### Dietary assessment

At the 9-month and 12-month visits, trained researchers will administer a 24-h dietary recall (referring to the preceding day) designed to estimate the quantity, type, brands, time of the day, and cooking methods (including a description of any recipes used, with amounts of raw ingredients) of all foods and drinks consumed by the infant. If the mother considers the previous day to have been atypical, she can substitute another day of the week that was more similar to the family’s eating routine.

The consistency of the food or drink (puréed, mashed, diced or whole), who fed the child (parent, child, or both), iron supplementation (including type, brand, time of day offered, and the amount taken) will also be collected.

All diet records will be entered into the dietary analysis in nutrition software to analyze energy, protein, fat, carbohydrate, iron intake and other micronutrients.

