### Randomization

After signing the consent form, participants will be sequentially numbered and have their names entered into a randomization list of three blocks and equal numbers, previously computer-generated (http://www.randomization.com) by blinded research staff.

Only at the time of the first intervention will mothers be aware of their group allocation. Assessment data will be collected by a different researcher from the one responsible for the intervention, blinded to the allocation group, in a different room.

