### Adherence

To ensure the families follow these instructions, a blinded researcher will conduct a phone call when the child is 7 months of age and ask some key questions (about food consistency when the child started to eat, and at 7 months; if the child takes food to mouth alone; and if the child receives food in spoon). A different researcher will analyze the answers and compare them with further data collected at the 9-month visit, in addition to a 24-h dietary record. These records will be collected during the home visit, by trained researchers. However, as some mothers might not be able to quantify food intake exactly, all participants will also be asked when they introduced a variety of different foods at the 9-month and 12-month visits. Questionnaires to assess adherence to self-feeding, breastfeeding practices, and introduction of complementary foods at 6 months will also be administered at the 9-month and 12-month visits. The rates of adherence will be analyzed. All participants will be included to the final analyses, regardless of having followed the method, since the analyzes will be made by intention-to-treat.

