### Questionnaires

Upon study enrollment, mothers will complete a sociodemographic questionnaire for calculation of the Brazilian Index Score (ABIPEME criteria) [64].

At 9 and 12 months, we will investigate feeding practices and the presence of choking. Eating behaviors and intestinal habits will be inquired specifically at the 12-month visit, as will the acceptability of the allocated CF approach to parents, focusing on “mess”, convenience, and cost.

Food intake will be assessed by a 24-h dietary recall. Data on oral hygiene habits will be collected through a questionnaire created for this study. Infant feeding behavior will be tested by the Baby Eating Behavior Questionnaire (BEBQ) [65] and Children Eating Behavior Questionnaire (CEBQ) [66]. Parental feeding perception will be assessed by the Caregiver Feeding Style Questionnaire (CFSQ) [67], while parental eating behavior will be assessed by the Dutch Eating Behavior Questionnaire (DEBQ) [68]. Finally, eating difficulties will be assessed with the Montreal Children’s Hospital Eating Scale (MCH-FS) [69].

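### Mothers who know their arm may choose which day the 24-h recall covers, which may bias recall-based secondary and adherence data by arm

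*Protocol article*

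**What the plan says.** The Dietary assessment section of the protocol article sets the reference day: at 9 and 12 months "trained researchers will administer a 24-h dietary recall (referring to the preceding day". It then allows an exception: "If the mother considers the previous day to have been atypical, she can substitute another day of the week that was more similar". The standard of comparison is how the family usually eats. The section does not define atypical, does not limit how far back the replacement day may lie, and does not ask for the swap to be recorded.

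The Questionnaires section makes this instrument the named source of intake: "Food intake will be assessed by a 24-h dietary recall". According to Dietary assessment, energy, macronutrients, iron and other micronutrients are computed from it, and these items are collected as well: "The consistency of the food or drink (puréed, mashed, diced or whole), who fed the child (parent, child, or both".

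Under Adherence, answers from the 7-month call are analysed by a different researcher, who will "compare them with further data collected at the 9-month visit, in addition to a 24-h dietary record". A further source is listed there: "Questionnaires to assess adherence to self-feeding, breastfeeding practices, and introduction of complementary foods at 6 months will also be administered" at the 9- and 12-month visits.

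On blinding, the Randomization section says "Only at the time of the first intervention will mothers be aware of their group allocation". It adds "Assessment data will be collected by a different researcher from the one responsible for the intervention, blinded to the allocation group".

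**The concern.** A recall tied to the preceding day has a reference day that the respondent does not choose. Once she may replace it, the recorded day depends on her judgement of what is normal. She makes that judgement after being taught one of three feeding methods, and assessor blinding does not reach it.

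The recall also captures what separates the arms. According to Study groups, the arms differ chiefly in food texture and in how far an adult takes part in the meal. The opportunity for selection is not the same in each arm. In the BLISS arm, a day on which an adult spoon-fed the child departs from the method. In the mixed arm, both ways of feeding are allowed as the child wishes, so hardly any day departs from it.

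At stake are the arm contrasts in energy and iron intake (iron intake is a named secondary analysis), in texture and in who fed the child, together with the recall's share of the adherence assessment. A day further back is probably also recalled less accurately, and the Adherence section already accepts that some mothers may not quantify intake exactly.

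**Working it through.** The plan gives no figure on this point, so there is none to reproduce. The check sets the provisions in order and then illustrates the possible size.

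**Order of events**

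1. Mothers learn their arm at the first intervention (Randomization), when the child is 5.5 months old (Study groups).
2. Recalls are taken at 9 and 12 months (Dietary assessment), so every recall follows unblinding of the mother.
3. The mother decides whether the preceding day was atypical and which day replaces it. The researcher's blinding does not affect that choice.
4. Adherence speaks of a 24-h record taken by trained researchers at the home visit. I read this as the same instrument, since Dietary assessment also calls the completed recalls diet records.

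**Illustration 1: recorded adherence.** Let p be the true share of days on the allocated method and s the probability that an off-method day is replaced by an on-method day. Both are assumed. Recorded share = p + (1 − p)s.

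| p | s = 0.10 | s = 0.25 | s = 0.50 |
|---|---|---|---|
| 0.70 | 73% | 77.5% | 85% |
| 0.90 | 91% | 92.5% | 95% |

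For example, 0.70 + 0.30 × 0.25 = 0.775.

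**Illustration 2: a yes/no feature of the day.** Suppose the feature is truly present on 50% of days in two arms, and swaps push the arms in opposite directions with probability s. The recorded shares are 0.5 + 0.5s and 0.5 − 0.5s, so the false difference equals s. With 48 per arm (Sample size) and a two-sided 5% comparison of proportions, the chance of a significant result in that direction is:

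| s | False difference | Chance |
|---|---|---|
| 0.05 | 5 points | 0.07 |
| 0.10 | 10 points | 0.16 |
| 0.20 | 20 points | 0.50 |
| 0.30 | 30 points | 0.85 |

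For s = 0.20 the shares are 0.60 and 0.40. The null standard error is √(2 × 0.25/48) = 0.102, so the critical difference is 1.96 × 0.102 = 0.200. That equals the false difference, hence a chance of 0.50. Opposite pushes are the unfavourable case.

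**Illustration 3: a continuous intake.** If a fraction s of an arm swaps and the chosen day differs from the true one by d SD, the arm mean moves by s × d, and the contrast moves by s₁d₁ − s₀d₀.

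- 20% v 10% swapping, d = 0.5 in both: (0.20 − 0.10) × 0.5 = 0.05 SD.
- 30% v 10%, d = 1 in both: (0.30 − 0.10) × 1 = 0.20 SD.
- 20% in both, d = +0.5 and −0.5: 0.10 + 0.10 = 0.20 SD.
- The same s × d in both arms: 0.

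All swap rates and displacements are assumed. The protocol supplies none.

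**The case against.** The strongest reply is that the swap criterion is the family's usual eating, not the allocated method. A reader might infer that the rule pulls the data towards what each arm was taught. The text does not establish that: a mother whose routine departs from her method could replace an on-method day with an off-method one. The direction is plausible but not shown. This objection stands.

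Three further inferences also go beyond the documents:

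- **That the recall is the only adherence check.** The Adherence section also uses the 7-month call, other 9-month data, and questionnaires at 9 and 12 months, none of them described as allowing a change of day.
- **That dietary variety is affected.** No section names the instrument for variety, and the dates on which foods were introduced are asked separately.
- **That the shift matches effects of interest.** No intake effect is stated. The only standardised effect is half an SD, for BMI, and 0.20 SD is less than half of that. It is about one standard error of a two-arm difference at 48 per arm (√(2/48) = 0.204).

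It can also be said that the advice on iron, energy, meals offered and foods to avoid is common to all arms, so a pull towards it may largely cancel for intake. Aiming one recall at a routine day is a defensible way to limit distortion from illness or travel. Unblinded maternal reporting would remain without the rule. These points narrow the concern without removing it. Texture and who fed the child are not common to the arms, and the swap adds selection of the day to whatever reporting bias already exists.

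Logging of swaps may be set out in operating procedures not shown here. The point therefore rests on the rule as stated, not on missing detail.

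**Conclusion.** The point holds as a weakness in a stated rule: a mother who knows the arm selects the day on which recall-based secondary data rest. It may bias contrasts in energy and iron intake, in food texture and in who fed the child, along with the recall's contribution to adherence. It also lengthens the recall gap for those who swap.

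Neither direction nor size can be fixed from the protocol. In the illustrations the effect runs from nothing, when the net shift is equal across arms, to 0.20 SD for a continuous intake, or 15 points on recorded adherence (70% to 85%), under strong assumed swapping.

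The primary outcome is untouched, because the z-scores come from measurements by blinded researchers. Adherence misclassification moves no child between analysis sets, since all participants are analysed by intention to treat. The correction is worth making because it is cheap, not because the main conclusion is in danger.

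**What to change.** Replace the substitution rule with three steps:

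1. Record the actual preceding day for every child at both visits.
2. Add a yes/no item on whether that day was atypical, with the reason (illness or travel, for example).
3. Run the recall-based analyses on all days, then repeat them without flagged days as a sensitivity analysis. This keeps the protection against unusual days that the swap was meant to give.

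Recruitment began in 2019 (Trial status), so some recalls may already have been taken under the present rule. For those, identify substituted days where possible, report their number by arm, and repeat the analysis without them.

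The cost is one changed instruction, one added item and slightly noisier single-day data. If the change comes mid-trial, two recall definitions will coexist. The analysis must then handle this, for example by recording which rule applied to each recall.
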